## 5 DATA MANAGEMENT

Astra Tech will coordinate Data Management activities.

Clinical Subject data will be collected via paper CRFs, and the collected data will be entered into a Clinical Data Management System called Oracle Clinical. Data will be recorded in the pCRFs only by authorized study site personnel at the investigational sites.

The study site personnel will be responsible for recording data on specified observations, tests and assessments specified in the protocol. Data editing for correction or clarification purposes will be made before the pCRFs are collected by the monitor and submitted for data entry at Astra Tech.

Data will be continuously entered and validated in Oracle Clinical at Astra Tech during the study. Should questionable data be detected during the validation process, written queries will be raised as result of this validation. The study site personnel are required to resolve any such queries.

At the end of the study, Astra Tech will perform final validation checks, including central consistency checks, after which Clean File will be declared and the database locked.

The study Data Management Plan will describe in greater detail the methods used to collect, check, and process clinical data. It will also clarify the roles and responsibilities of the various functions and personnel involved in the data management process.

## 6 STATISTICAL METHODS AND DETERMINATION OF SAMPLE SIZE

### 6.1 Statistical evaluation – general aspects

When using the terminology descriptive statistics it is meant that the number of subjects, mean, median, standard deviation, minimum and maximum values will be presented for continuous data and frequencies and percentages for categorical data. If nothing else is stated, descriptive statistics will be given for each variable in the study.

A p-value below 5% is called statistically significant even though it is recognized that multiple secondary hypotheses will be tested.

A comprehensive Statistical Analysis Plan (SAP) may be prepared before database lock. If prepared, the Statistical Analysis Plan will be kept as an appendix to the Data Management Plan.

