### 2.2 Secondary objectives

The secondary objectives of the study are....

....to observe and compare clinical efficacy by means of postoperative infection rates, use of postoperative antibiotics, length of hospital stay and health status for patients transfused with Sangvia® blood, no blood and/or allogeneic blood.

....to observe and compare clinical efficacy by means of systemic postoperative haemoglobin levels for patients transfused with Sangvia® blood, no blood or allogeneic blood.

....to collect details in health care utilisation (medications, in-patient service use, blood management) that would allow a calculation and comparison of cost-consequences applying either alternative in the blood management and from the perspective of the payer

....to observe and compare safety by means of adverse events, highlighting renal failures and events potentially related to transfusion, body temperature and other clinical complications for patients transfused with Sangvia® blood, no blood or allogeneic blood.

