#### 4.3.1.2 Derivation or calculation of variable

Each variable will be evaluated and presented separately and an overall post-operative infection rate will also be calculated.

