##### 4.3.2.2 Derivation or calculation of variable

Use of post-operative antibiotics will be expressed in percentage per treatment arm, i.e. number of subjects with post-operative antibiotics/total number of subjects. The total number of days and dose registered in the MED log for post-operative antibiotics will also be presented per treatment arm.

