## 6.2 Description of outcome variables in relation to objectives and hypotheses

The primary variable, transfusion rate, will be measured as the proportion ( $\pi$ ) of patients in each treatment group that is receiving allogeneic blood transfusion of the total number of patients in each treatment group. The hypothesis to be tested is:

$$H_0 = \pi_s = \pi_c$$

versus

$$H_1 = \pi_s \neq \pi_c$$

Where:

$\pi_s$  = Proportion patients treated with Sangvia® that require allogeneic blood transfusion in addition to Sangvia® transfusion.

$\pi_c$  = Proportion patients in the control group that require allogeneic blood transfusion.

The hypothesis will be tested using the Fischer Exact Test. The hypothesis will be rejected if the p-value is  $\leq 0.05$ .

Secondary objectives will be tested using similar hypotheses. The total and variable specific proportion values for infection rate, use of post-operative antibiotics and adverse events will be tested between the groups using the Fischer Exact Test. Continuous variables (e.g. post-op Hb values) will be compared and tested using the Wilcoxon Rank Sum test. Laboratory blood markers will also be evaluated for changes over time within each treatment group and this change will be tested using the Wilcoxon Signed Rank test.

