## 6.3 Description of analysis sets

The study will be analyzed using a Per Protocol (PP) and an All Patient Treated (APT) approach. Subjects fulfilling the inclusion criteria but none of the exclusion criteria and have been treated according to the protocol without any major deviations (e.g. wrongful transfusion decision of bank blood) will be included in the PP analysis set. All patients will be included in the APT analysis set. Treatment efficacy related conclusions will be based on the results from the PP analysis and demography and treatment safety related conclusions will be based on the results from the APT analysis.

Subgroup analyses of type (primary and secondary) and complexity (easy < 1 hour, medium 1-2 hours and complex > 2 hours) of surgery will be performed as well as analyses per clinic and per blood transfusion type (none, autologous, allogeneic and combinations).

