## 6.4 Method of statistical analysis

Fischer Exact test will be used to test frequencies of dichotomous response variables. The non-parametric Wilcoxon Rank Sum test will be used to test differences in continuous response

variables between the parallel treatment groups. Wilcoxon Signed Rank test will be used to test differences over time within each treatment group. P-values equal to or below 0.05 are considered as statistically significant.

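### The protocol calls every secondary p-value below 5% statistically significant, across at least 19 clinical-efficacy comparisons, with no hierarchy, gate or exploratory label

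*Protocol*

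**What the plan says.** Section 6.1 sets the rule and acknowledges the difficulty in the same sentence: "A p-value below 5% is called statistically significant even though it is recognized that multiple secondary hypotheses will be tested". Section 6.4 gives a flat threshold for all tests, "P-values equal to or below 0.05 are considered as statistically significant", and the statistical methods paragraph of the synopsis repeats it.

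Section 2.2 describes the first group of secondary objectives as being "to observe and compare clinical efficacy by means of postoperative infection rates, use of postoperative antibiotics, length of hospital stay and health status", and a further secondary objective uses the same efficacy language for post-operative haemoglobin (Hb). Section 6.2 then says "Secondary objectives will be tested using similar hypotheses" and names the tests: Fisher's exact test for proportions and the Wilcoxon rank sum test for continuous variables. For the proportions it specifies that "The total and variable specific proportion values for infection rate, use of post-operative antibiotics and adverse events will be tested between the groups".

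On the components of infection, section 4.3.1.2 says "Each variable will be evaluated and presented separately and an overall post-operative infection rate will also be calculated". Section 6.3 adds that "Treatment efficacy related conclusions will be based on the results from the PP analysis", without limiting those conclusions to the primary variable.

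The protocol contains no order of testing, no correction, no condition on the primary result and no exploratory label for the secondaries. Section 6.1 makes a statistical analysis plan optional.

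**The concern.** This is a stated rule, not a matter left open for the analysis plan. Leaving secondary tests unadjusted is ordinary practice when they are presented as exploratory. Here they are described as comparisons of clinical efficacy, given formal hypotheses, and called statistically significant one by one at 5%.

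Section 1 says that the study is meant to prove clinical benefit. Suppose the transfusion-rate test fails. One nominal p-value on infection, antibiotic use, length of stay, Hb or EQ-5D could then still be reported, in line with the protocol, as a statistically significant efficacy result. Nothing tells the reader how far to discount it. What is at stake is the credibility of secondary claims, not the primary conclusion.

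**Working it through.** **The plan's own figures.** The protocol states no number of secondary tests and no family-wise error rate, so there is no figure on this point to reproduce. The one related figure is the primary sample size in section 6.5:

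N = (1.96 + 1.2816)² × 4 × 0.14 × 0.86 / (0.07 − 0.21)² = 258.2

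This agrees with the stated 260. The calculation uses the transfusion rates alone. No secondary test enters it.

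**Count of between-arm secondary efficacy tests.**

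| Endpoint | Source | Tests |
|---|---|---|
| Infection: clinical symptoms, SIRS, wound, CRP, LPC, overall | 4.3.1, 6.2 | 6 |
| Antibiotic use, proportion | 4.3.2.2 | 1 |
| Length of stay, total | 4.3.3.2 | 1 |
| Hb: four post-operative times, absolute and change from baseline | 4.3.4 | 8 |
| EQ-5D: day 4, month 2, change | 4.5.1.2 | 3 |
| **Total** | | **19** |

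This leaves out antibiotic days and dose, stay by care facility or clinic, adverse events, within-arm signed rank tests, subgroups and comparisons by transfusion type.

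**Chance of at least one p < 0.05 with no true effect.** If the tests are independent:

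- Either direction: 1 − 0.95^19 = 1 − 0.377 = 0.62.
- Favouring the device only (2.5% per test): 1 − 0.975^19 = 1 − 0.618 = 0.38.

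The tests are correlated, and the protocol does not say how strongly. With 19 two-sided 5% z-tests sharing one common correlation, which is an assumption:

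| Assumed correlation | Either direction | Favouring the device |
|---|---|---|
| 0 | 0.62 | 0.38 |
| 0.3 | 0.53 | 0.27 |
| 0.5 | 0.41 | 0.20 |
| 0.8 | 0.22 | 0.11 |

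**Effect of the overlaps.** Absolute Hb and change in Hb share data, and overall infection is built from its five components. Removing the four Hb change tests and the overall infection test leaves 19 − 4 − 1 = 14. Under independence this gives 1 − 0.95^14 = 0.51 in either direction and 1 − 0.975^14 = 0.30 in the device's favour.

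**Effect of the named tests.** Seven of the 19 are Fisher exact tests, which are conservative. With 150 per arm, the true size of a nominal 5% test is about 1.2% at an assumed event rate of 2%, 2.4% at 5% and 3.3% at 10%. A null simulation used 7 Fisher and 12 rank sum tests, with Hb and EQ-5D contrasts built from shared data. It covered assumed event rates of 2% to 30% and correlations from none to very high. It gave about 41% to 53% in either direction and about 23% to 30% in the device's favour, inside the ranges above.

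**Against a controlled rule.** Bonferroni over 19 tests would require 0.05/19 = 0.0026 per test. A fixed sequence at 5% per step also keeps the family-wise error at or below 5%.

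**The case against.** Much of the case on the other side stands.

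- **The primary is protected.** Section 6.2 sets one primary hypothesis with one test, and section 6.5 sizes the study on it. A reader might infer that the trial's main error rate is inflated. It is not.
- **No promise is broken.** The protocol sets 5% per p-value and never offers 5% over the secondary family. It would be wrong to say that a stated family-wise rate is exceeded by some multiple.
- **The size is easily overstated.** A reader might infer a 4 in 10 chance of a spurious claim for the device. That figure counts either direction at an assumed correlation of 0.5. Counting only device-favourable results at the same correlation gives about 2 in 10, before allowing for Fisher's conservatism.
- **The count includes near-duplicates.** This is true of Hb and overall infection. Correlation allows for it in part, and the count of 14 shows that it does not remove the problem.
- **Efficacy may mean the primary only.** Sections 1.2 and 2 tie efficacy to the transfusion rate, and section 3.2 calls length of stay and Hb multi-factorial. A reader might infer that section 6.3 turns every secondary p-value into an efficacy conclusion. Its text does not say so. Section 2.2 nevertheless uses the words clinical efficacy for these endpoints, and nothing in section 6.3 excludes them.
- **The multiplicity is disclosed, and the study is post-marketing.** Disclosure is better than silence, but it gives no rule for interpretation. An analysis plan could add labels, but it is optional and the protocol has already fixed the significance rule.

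**Conclusion.** The point holds as a weakness in how secondary results are declared. Followed as written, the protocol allows a chance finding among at least 19 overlapping comparisons to be called a statistically significant clinical-efficacy result, even after a failed primary.

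The size is a range: about 22% to 62% for at least one p-value below 0.05 in either direction, and about 11% to 38% in the device's favour. It rests on a count of 19, no true effect on any secondary, and assumed equal correlations of 0.8 down to 0. None of these correlations comes from the protocol, and Fisher's conservatism would lower the figures. Even the lowest device-favourable value, 11%, is above the 2.5% that a single two-sided 5% test allows in that direction. The conclusion therefore does not depend on one choice of correlation.

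This should be corrected, but it does not threaten the primary analysis.

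**What to change.** In sections 6.1 and 6.4 and in the synopsis, state that only the transfusion-rate hypothesis in section 6.2 is confirmatory, at two-sided 5%. State that all secondary comparisons are exploratory and are reported as estimates with 95% confidence intervals and nominal, unadjusted p-values. Amend the sentence in section 6.2 on testing secondary objectives to match.

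If the sponsor wants a secondary efficacy claim, prespecify a short fixed sequence with one contrast per endpoint, for example a single Hb time point rather than eight comparisons. Each step is tested at 5%, and only after a significant primary and a significant preceding step. The order must be set before any comparative results are known.

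The cost is protocol wording: no extra patients, no extra data and no loss of primary power. The downside is that isolated secondary p-values can no longer be claimed as statistically significant efficacy results.

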#### 6.1.1 Demographics and other baseline characteristics

Demographics and other baseline characteristics will be presented by means of descriptive statistics.

#### 6.1.2 Covariates and prognostic variables

Bleeding volume or complexity of surgery, i.e. surgery time, are considered to possibly influence outcome of the primary variable why stratification for either primary or secondary/revision hip surgery will be made at each recruiting clinic to ensure equal distribution in the two groups. Subgroup analyses of type (primary and secondary) and complexity (easy < 1 hour, medium 1-2 hours and complex > 2 hours) of surgery are planned to further investigate the correlation between the primary outcome and these factors.

Age is also an potential factor that may have an impact on the outcome of the primary variable. It is however considered that randomization as such will ensure approximately equal age distribution in the two treatment groups. Differences in age between the treatment groups will be evaluated and tested using Wilcoxon rank sum test in the analysis.

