#### 6.1.4 Multi-centre

This study is a multi-centre study and there is no a priori reason to suspect that there will be any qualitative differences between the centres. However, local treatment routines at different clinics

are considered to potentially affect the outcome of the primary variable why stratification for each clinic will be made. This is considered to ensure equal distribution between test and control group patients why primary statistical analysis will not include centre in the model. The result of the primary variable will however be presented by centre as part in subgroup analyses.

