## 6.5 Determination of sample size

The primary variable and objective is the base for the sample size calculation. The sample size formula used is referred to in Lachin 1981.

$$N = \frac{(Z_{\alpha} + Z_{\beta})^2 4\bar{\pi}(1 - \bar{\pi})}{(\pi_s - \pi_c)^2}$$

Where:

N = total number of patients

$Z_{\alpha} = 1.96$  ( $\alpha = 0.05$ )

$Z_{\beta} = 1.2816$  ( $1 - \beta = 0.90$ )

$$\bar{\pi} = \frac{\pi_s + \pi_c}{2}$$

An estimation normal use of allogeneic blood of 21% is based on reported values in the literature. It is acknowledged that in revision surgery a higher percentage of allogeneic blood transfusions is seen than in primary total hip replacements. Because revision patients requiring serious bone grafting are excluded, the percentage of revision patients is expected to be just slightly higher than for the average primary total hip. A high number of revision, e.g. a maximum of 30%, in the total group of patients is considered to have limited effect of the total transfusion rate but are accounted for in the 21% assumed for the total group. The expected values of transfusion rate in the Sangvia® group is estimated to lie around 7%. Accordingly, imputing the values for the estimated transfusion rates in the test and control group generates a mean transfusion rate value of 14%. The sample size necessary for detection of this expected difference in transfusion rate frequency is calculated to 260 patients (5% significance level, two-sided hypothesis, 90% power). Additional 40 patients will be included in the study to compensate for drop-out. In summary, 300 patients will be included in total and 150 in each treatment group.

The transfusion rate of bank blood is considered to vary dependent on type and complexity of surgery. Greatest normal use and differences between the groups are expected in the subgroup with medium (surgery duration 1-2 hours) to complex (surgery duration more than 2 hours) surgery complexity why power are considered to be adequate for the planned subgroup analyses in these groups.

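### The surgery-type subgroup analysis includes no treatment-by-type comparison, so it cannot show whether the effect differs between primary and revision surgery

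*Protocol*

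**What the plan says.** Section 6.1.2 states that subgroup analyses of type (primary and secondary) and complexity of surgery "are planned to further investigate the correlation between the primary outcome and these factors". Section 6.3 makes this a commitment: analyses of type and complexity "of surgery will be performed as well as analyses per clinic", and by type of transfusion received. On centres, section 6.1.4 keeps centre out of the primary model and adds: "The result of the primary variable will however be presented by centre as part in subgroup analyses".

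Section 6.4 names Fisher's exact test for dichotomous responses and sets one threshold for everything: "P-values equal to or below 0.05 are considered as statistically significant". Section 6.2 applies that test to the single overall hypothesis on the transfusion rate.

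The protocol contains no treatment-by-subgroup interaction or homogeneity test, and it nowhere calls the subgroup results exploratory or descriptive. The multiplicity remark in section 6.1 covers secondary hypotheses only. The same section makes a statistical analysis plan optional.

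**The concern.** The protocol wants to know how the primary outcome relates to surgery type, and randomisation is stratified by that factor. With the tools it names, the analysis becomes one Fisher test among primary operations and another among revisions. Each asks whether there is an effect in that group. Neither asks whether the two effects differ.

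The groups are of unequal size by design, with revisions expected to make up at most 30%. The smaller one will often miss significance even when the device works equally well in both. The report could then say that benefit was shown in primary surgery but not in revision surgery, when the contrast reflects only subgroup size. At stake are statements about who benefits, not the primary conclusion.

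This point concerns surgery type. The groupings by operation time and by transfusion received are formed after randomisation and are set aside here.

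**Working it through.** **Inputs, all from section 6.5 unless marked**
- Control rate: "An estimation normal use of allogeneic blood of 21" per cent. The Sangvia "group is estimated to lie around 7" per cent.
- Design: "5% significance level, two-sided hypothesis, 90% power".
- Size: the total "is calculated to 260 patients"; 40 are added for drop-out, giving 300, or 150 per arm.
- Revision share: 30% is named as a maximum; 20% is my assumption for a lower share.
- Control risk in revisions: expected to be only slightly above primary surgery, with no figure. Base case: 21% in both types. Assumed sensitivity values: 25% and 30%.
- Test: two-sided Fisher exact, p ≤ 0.05 (section 6.4).

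**The plan's own figure**

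N = (1.96 + 1.2816)² × 4 × 0.14 × 0.86 / 0.14² = 10.508 × 0.4816 / 0.0196 = 258.2, against 260 stated. The figure is reproduced. Exact Fisher power for the overall comparison is 88.8% at N = 260 and 93.1% at N = 300.

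**Discordance under a uniform effect**

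Let a be the power in primary surgery and b the power in revision surgery, each by exact enumeration of Fisher's test at 21% v 7%. The strata are independent, so

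P(one significant, the other not) = a(1 − b) + b(1 − a).

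| N | Revisions | Per arm, primary / revision | a | b | a(1 − b) | b(1 − a) | Discordant |
|---|---|---|---|---|---|---|---|
| 300 | 30% | 105 / 45 | 0.802 | 0.380 | 0.497 | 0.075 | 57.2% |
| 260 | 30% | 91 / 39 | 0.733 | 0.321 | 0.498 | 0.086 | 58.4% |
| 300 | 20% | 120 / 30 | 0.856 | 0.197 | 0.687 | 0.028 | 71.6% |
| 260 | 20% | 104 / 26 | 0.797 | 0.183 | 0.651 | 0.037 | 68.8% |

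At 30% revisions, about 50 of the 57-58 percentage points are trials in which only primary surgery is significant. Both types are significant in 30.5% (N = 300) or 23.5% (N = 260) of trials, and neither in 12.3% or 18.1%. A normal approximation in place of Fisher's test gives 51% (N = 300) and 54% (N = 260) discordant.

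**Sensitivity to a higher revision risk (assumed), 30% revisions**

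The overall control rate is held at about 21% and the risk ratio at 1/3 in both types.
- Revision control risk 25%, primary 19.3% (0.3 × 0.25 + 0.7 × 0.193 = 0.210): discordant 53% (N = 260) and 52% (N = 300).
- Revision control risk 30%, primary 17.1% (0.3 × 0.30 + 0.7 × 0.171 = 0.210): discordant 50% and 47%.

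**Why clinics need different handling**

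Six clinics averaging 50 patients have 25 per arm (equal clinic size is an assumption). Expected test-arm events per clinic are 25 × 0.07 = 1.75. The chance of none is 0.93²⁵ ≈ 0.16. At least one of the six clinics has no test-arm event with probability 1 − (1 − 0.163)⁶ ≈ 0.66. Treatment-by-clinic odds ratios would then often be zero or inestimable, and a homogeneity test across clinics would be unreliable.

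**The case against.** The strongest reply is that an interaction test, a display of estimates and an exploratory label are ordinary content of a statistical analysis plan, and that no sentence orders Fisher's test within each surgery type. Section 6.2 applies it to one overall hypothesis, and section 6.4 is a general statement. The aim in section 6.1.2 can also be read as prognostic (whether transfusion varies with type of surgery), and its wording already sounds exploratory.

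Part of this stands. Within-type testing is an inference, though a natural one: the protocol commits to the analyses, names one test and one threshold for a dichotomous response, and does not firmly defer the matter. Section 6.5 also discusses treatment-group differences and power inside subgroups. That sentence concerns only medium and complex operations, so it shows how subgroup analyses are meant to be read but makes no claim about surgery type.

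A reader might infer more than the protocol supports:
- *That the two types would show effects in opposite directions.* Discordance here means significant in one and not significant in the other. Significant effects in opposite directions have essentially zero probability under the assumed rates.
- *That discordance is certain to occur in most trials.* It falls to about half, or slightly below, if revision control risk is 25-30%.
- *That a Fisher test is prescribed in every clinic.* Section 6.1.4 says only that results are presented by centre, section 6.3 names no test for clinics, and the aim in section 6.1.2 refers to type and complexity, not clinic.
- *That eight subgroup tests inflate the trial's false-positive rate.* Six of the eight would be clinic tests that the protocol does not state. It has one primary hypothesis, whose type I error is untouched.

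**Conclusion.** The point holds for surgery type. The plan commits to a subgroup analysis but provides no comparison that can answer whether the effect differs between primary and revision surgery. Under a uniform 21% v 7% effect, separate tests disagree in about 57-58% of trials at the 30% revision maximum and in about 70% at 20% revisions, mostly because the revision group is small. With an assumed revision control risk of 25-30%, the range is about 47-53%.

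These figures assume equal allocation within type, 260 to 300 analysed patients and Fisher's test in each type. The primary test, its error rate and the sample size are unaffected. The matter should be corrected because statements about which patients benefit would otherwise rest on subgroup size.

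**What to change.** In sections 6.1.2 and 6.3, state that:
- consistency of the treatment effect across surgery type is judged by one treatment-by-type homogeneity test (Breslow-Day, or an interaction term in a logistic model);
- the risk difference with its 95% CI is shown for each type, without within-subgroup p-values;
- these results are exploratory;
- results by clinic are descriptive only (counts and risk differences with CIs), with no test per clinic and no homogeneity test across clinics, because events are too sparse.

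The text should note that the homogeneity test works on the odds ratio while the display uses risk differences.

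The cost is a few sentences and standard output from data already collected. The homogeneity test will have low power, so a non-significant result must not be read as proof of consistency. No claim could rest on the p-value of a single subgroup.
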